### Procedures

#### Recruitment and Randomization

An experienced fieldwork technician with the help of two more experts recruited participants in collaboration with the Barcelona school system. We first obtained permission from the boards of several schools in Barcelona to inform them about the trial. Then, we provided the schools with a recruitment fllier to assess willingness to collaborate and grant us permission to contact interested families by telephone. Families interested in participating contacted us through the school and filled out a form with their telephone number. Trained personnel contacted the parents and explained the study in detail. Fieldworkers verified the eligibility criteria of each candidate. We performed age-, gender-, and maternal education-stratified random computerized sampling within each school to assign adolescents to one of the two groups. In order to avoid contamination, we gave the walnuts for free to the corresponding group and asked participants to consume them at home.

#### Implementation and Adherence

All families received a basic guide to the seasonal fruits needed to follow healthful diet recommendations (eating a piece of fresh fruit every day) in order to ensure implementation and adherence. The control group received the same instructions, including the general recommendation to eat a piece of fresh fruit every day, as well as feedback to encourage them to remain in the study. Families in the walnut intervention group received additional instructions on how to encourage participants to eat their daily allotment of walnuts, which we supplied for free in sachets of 30 grams; no other recommendations were given. We asked parents to supervise the intervention by checking the subject's adherence to the walnut consumption. To evaluate adherence to the intervention, the Survey Monkey web-based platform was used weekly. Participants in the walnut group were contacted in the middle of the study, and recipes for dishes containing walnuts were provided; they were also asked to report their daily walnut consumption weekly, using the Survey Monkey platform and to cross off the days they had or hadn't eaten the allocated amounts of walnuts on a calendar, in order to evaluate adherence to the intervention. Moreover, the participants were eligible for a periodic raffle for completing the Survey Monkey reports weekly. The prize was entrance tickets to a science museum.

## Results

### Dietary Assessment

A food frequency questionnaire (FFQ), validated for the Spanish population (24) and adapted to the adolescent range, was administered to all adolescent participants at baseline and at the end of the intervention (after 6 months). Additionally, a short FFQ was completed every 3 months. We added the measurement of dietary patterns to our study in order to control for these factors in secondary analyses, since diet can be changed after a nutritional intervention.

### Neuropsychological and Behavioral Testing

Multiple primary endpoints concerning the neuropsychological and behavioral development of adolescents was assessed before randomization, at baseline (pre-intervention) and after 6 months (post-intervention). A total of six tests (six primary outcomes) developed for assessing children and adolescents were used to measure changes from baseline in the main score for each of the tests for neuropsychological (working memory, attention, fluid intelligence and executive function) and behavioral (socio-emotional and ADHD symptoms) outcomes (25). The first primary outcome measurement was the N-back task, which is a computer-based test assessing working memory using series of numbers. The stimulus appears in the laptop screen one by one. Children were invited to press a button in the keyboard when the stimulus is the same as the previous one in the 1-back level. In 2-back, they were required to press the button when the stimulus in the screen is the same as the one presented two trials back. In 3-back, they had to press when the stimulus was the same as the one presented three trials back. The outcome is *d*: *d* prime (*d'*) = *z* (hit rate) - *z* (false alarm rate) (26). The second measurement was the Attention Network Test (ANT), also known as the flanker test, which is also a computerized test aimed at examining sustained attention based on reaction times to target stimuli. The test provides several attention functions (orienting, alerting, and conflicting); however, hit reaction time standard error is the “gold standard” to measure sustained attention, since it is the reaction time variability during the attention task (27, 28). The third measurement was the inductive reasoning subtest (fluid intelligence) of the Tests of Primary Mental Abilities (PMA-R, the Spanish adaptation) (29). The fourth measurement, the Roulettes Task (adapted from the Cups Task), was a gambling task aiming to assess risky decision making, i.e., whether the participants adjust their risky behavior according to the probabilities and importance of the outcome (cognition influenced by emotion) (30). The fifth measurement was the self-reported version of the Strengths and Difficulties Questionnaire (SDQ). It consists of 25 questions, organized in a general score of problem behavior and five subscales aimed to assess emotional symptoms, conduct problems, hyperactivity/inattention, peer relationship problems and pro-social behavior (31). The sixth measurement was the Attention Deficit Hyperactivity Disorder (ADHD) DSM-IV form list. We asked the teacher of the adolescent to answer 18 multiple-choice questions in order to rate his/her ADHD performance. The scores were transformed into a number of symptoms and diagnostic criteria for ADHD and inattentive and hyperactive subtypes. The administration of these neuropsychological tests was carried out by a trained psychologist and fieldwork technicians, and the tests were hold at the schools after securing comfortable and quiet quarters.

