We hypothesized that walnut supplementation for 6 months would enhance neuropsychological and behavioral (socio-emotional) development among healthy teenagers. We further hypothesized that a walnut intervention for 6 months would increase omega-3 PUFA tissue availability.

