## Methods and Materials

### Trial Design

WALNUTs (WSS) is a multi-school, parallel (two-group), controlled, 6-month superiority randomized clinical trial in a large population-based sample aiming to include 800 healthy teenagers in Barcelona, Spain. After data collection, 771 participants were equally randomized in two groups (386/385), but because of some exclusions post-randomization, 748 were finally included. Study subjects were randomly assigned to two intervention groups just after baseline assessments: the walnut group (*n* = 370, consuming walnuts daily and advised to follow general healthful eating recommendations, such as eating a piece of fresh fruit every day) or control group (*n* = 378, not consuming walnuts and advised also to follow the same general healthful eating recommendations). They were assessed at baseline and after the intervention by several internationally validated neuropsychological tests and behavioral rating scales. Due to the project's budget limitations, a random subsample of 200 adolescents per group of intervention (*n* = 400) were targeted to measure changes in omega-3 PUFA biomarkers. We finally got 270 participants, 139 in the walnut group and 131 in the control group. All participants randomized to the walnut group received 30g/day of kernel walnuts to be incorporated into their diet for free. The type of walnuts selected, Californian walnuts, is estimated to contain about 9 g of ALA per 100 g (20, 21). There is evidence that young Spanish subjects between 10–13 and 14–17 years of age consume on average 5.7 g (SD 24.5 g) and 6.1 g (SD, 20.8 g) of nuts daily (22), which supports the feasibility of our trial design. Figure 1 shows the project's design and structure.

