### Eligibility Criteria

The participants eligible were adolescents aged between 11 and 16 years attending regular schools in Barcelona. Originally, the study protocol was designed to recruit adolescents aged 12–15 years; however, the schools facilitated participant recruitment through the classes, and there were children a bit younger and older that we did not want to exclude if they were willing to participate in the study. Exclusion criteria include those consuming supplements of omega-3 PUFAs regularly, eating walnuts on a daily basis, and/or having an allergy to walnuts and/or gluten. Subjects were excluded also if they reported lactose intolerance or an allergy to cereals, dried fruits, peanuts, soy, sesame, or sulfites, since the walnut industry manipulates these products and there could be traces of them in the walnut packages. Eligible candidates who were siblings of family units were randomized and allocated to the same group and analyzed as clusters.

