### Sample Size

Prior to data collection, the statistical power of the study for neuropsychological outcomes was based on 400 participants per group. Six primary outcomes were considered: the N-back task, the Attention Network Test (ANT), the Tests of Primary Mental Abilities (PMA-R, the Spanish adaptation), the Roulettes Task (adapted from the Cups Task), the Strengths and Difficulties Questionnaire (SDQ), and the Attention Deficit Hyperactivity Disorder (ADHD) DSM-IV form list. The cognitive outcomes with mean values of 100 (SD 15) units corresponding to the standard values of neuropsychological scores in the general population (23) were considered, with a correlation between them of 0.25. The targeted intervention effect was a change of 3 units, based on previous studies in adult samples (16, 18). We considered a type I error of 0.05 and corrected calculations for multiplicity using the Benjamini-Hochberg method. A 10% loss of follow-up was assumed. Additionally, we assumed that the final models had an R^2^ of 20%. With all these considerations, the study would have 95% power to detect the effect with at least one outcome, 90% to detect the effect with at least two, 80% to detect the effect with at least 3, 70% to detect the effect with at least 4, 55% to detect the effect with at least 5, and 31% to detect the effect with all six outcomes. Similar power calculations can be made from the final participation sample of 748 participants.

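### The ADHD primary outcome reduces 18 teacher ratings to a symptom count and diagnostic criteria in a healthy, unselected sample, which makes it less sensitive than the 0.20 SD effect the power plan applies to all six outcomes

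*Protocol article*

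**What the plan says.** All references are to the protocol article.

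- **Instrument and scoring** (Neuropsychological and Behavioral Testing): "We asked the teacher of the adolescent to answer 18 multiple-choice questions in order to rate his/her ADHD performance". Then: "The scores were transformed into a number of symptoms and diagnostic criteria for ADHD and inattentive and hyperactive subtypes". No other ADHD score is described.
- **Endpoint** (same section): the six tests are "used to measure changes from baseline in the main score for each of the tests". The main ADHD score is not identified.
- **Population**: the trial is "aiming to include 800 healthy teenagers in Barcelona, Spain" (Trial Design). "The participants eligible were adolescents aged between 11 and 16 years attending regular schools in Barcelona" (Eligibility Criteria). The exclusions concern supplements, walnut intake, allergies and intolerance. None concerns ADHD, and no symptom level is required at entry.
- **Hypothesis** (Background): the intervention "would enhance neuropsychological and behavioral (socio-emotional) development among healthy teenagers".
- **Power** (Sample Size): "Six primary outcomes were considered", ADHD among them. The inputs are mean 100, SD 15, a 3-unit change, correlation 0.25 and Benjamini-Hochberg correction. The ADHD score has no mean, SD or effect of its own.
- **Analysis** (Data Analysis): multivariable linear regression, two-sided 0.05, with a nominal and a corrected p-value reported for each primary endpoint.

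**The concern.** A symptom count records only whether each item passes a cut-off, and a diagnosis cuts that count again. An adolescent whose ratings improve without crossing a cut-off contributes nothing. In a sample not chosen for ADHD symptoms, part of any improvement probably lies in that lower range.

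The power plan makes no allowance for this. Each primary endpoint will also be reported with its own p-value, so a null ADHD result will be read on its own as evidence about attention symptoms. What is at stake is the sensitivity of one outcome in six, and the power to show an effect on five or all six.

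**Working it through.** **1. The plan's own power figures.** The design "was based on 400 participants per group"; with 10% loss, 400 × 0.9 = 360 per group. Without the R² gain, the expected test statistic is 3 / (15 × √(2/360)) = 2.683, and single-outcome power at two-sided 0.05 is 76.5%. Six equally responsive outcomes (correlation 0.25, Benjamini-Hochberg, 400,000 simulated trials) give:

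| Power (%) for at least | 1 | 2 | 3 | 4 | 5 | 6 |
|---|---|---|---|---|---|---|
| Stated | 95 | 90 | 80 | 70 | 55 | 31 |
| R² = 0 | 95.4 | 90.6 | 83.4 | 72.4 | 55.8 | 31.3 |
| R² = 20% | 98.4 | 96.3 | 92.7 | 85.9 | 73.0 | 47.9 |
| R² = 0, ADHD at half effect | 93.5 | 86.5 | 76.3 | 61.3 | 39.9 | 14.1 |
| R² = 0, ADHD cannot respond | 93.5 | 86.3 | 75.3 | 58.5 | 33.3 | 1.9 |

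The stated figures lie close to the R² = 0 row, in which ADHD receives the same 0.20 SD effect as the rest. The mismatch with the stated R² of 20% is a separate matter.

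**2. Count against sum.** The documents give no ADHD distribution, so these inputs are assumptions: 18 items scored 0-3; a symptom counted at 2 or above; share at 1 or above three times the share at 2 or above (capped at 60% or more, so the cap does not alter the three-fold ratio here); share at 3 one third of it; latent improvement 3/15 = 0.20 SD; 360 per group; t-test at two-sided 0.05 before multiplicity correction; 1,500 replicates. Each cell shows item loadings 0.7 / 0.8.

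| Item endorsement | Share with zero symptoms (%) | Power, count (%) | Power, sum (%) | Difference (points) |
|---|---|---|---|---|
| 20% | 28.6 / 38.8 | 63.5 / 60.3 | 71.6 / 71.5 | 8.1 / 11.2 |
| 10% | 49.3 / 58.8 | 53.7 / 48.7 | 63.4 / 59.9 | 9.7 / 11.2 |
| 5% | 67.1 / 74.1 | 41.7 / 38.5 | 54.9 / 51.0 | 13.2 / 12.5 |
| 3% | 76.8 / 82.1 | 35.1 / 29.1 | 45.1 / 40.0 | 10.0 / 10.9 |

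**3. How much of the shortfall is due to scoring.** Measured from 76.5%, loading 0.7:
- At 5% endorsement the count loses 76.5 − 41.7 = 34.8 points. The sum also loses 76.5 − 54.9 = 21.6 of these, so 13.2 are due to counting.
- At 20% endorsement the count loses 76.5 − 63.5 = 13.0 points. The sum loses 76.5 − 71.6 = 4.9, so 8.1 are due to counting.

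The rarer the symptoms, the larger the part that no rescoring recovers.

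**4. Final sample, wider assumptions.** For 370 vs 378, power = Φ(d × √(370 × 378 / 748) − 1.96), and the root is 13.67. An observed d of 0.20 gives 78%. With the three-fold assumption of step 2, loadings 0.6-0.85 and endorsement 3-20%, the count shows d of about 0.10-0.17 and the sum 0.12-0.19. At these rounded values the formula gives 28-64% and 37-74%.

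The three-fold assumption sets how much rating lies below the cut-off for the sum to recover. Varying it gives about 28-68% for the count and 31-73% for the sum. The gain is about 1 to 13 points, and the count's relative efficiency (d count / d sum)² is about 0.69 to 0.99. That is like discarding 1% to 31% of the sample. A diagnosis-type cut-off gives roughly 8-49%.

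**The case against.** **The SAP may settle it.** The article does not name the main ADHD score, and a SAP not shown may do so. That silence alone would be no finding. But the article describes only one route from the 18 answers to a score, and both of its products are coarser than the answers.

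**The floor is not documented.** A reader might infer that most scores sit at or near zero, so that little improvement can be detected. The documents do not support this. They report no ADHD distribution, they do not exclude adolescents with symptoms, and the assumed share at zero runs from 20% to 85%. Participants at zero can also gain symptoms over six months, so a between-group difference can arise through less worsening.

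**A null result would not be the scoring's doing.** A reader might also infer that a null ADHD result would reflect the scoring rather than walnuts. That is too strong. With 31-73% power, the graded sum would itself miss a 0.20 SD effect 27-69% of the time.

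**The trial-level effect is small.** Success requires any one of six endpoints. Even if ADHD could not respond at all, power for at least one falls only from 95.4% to 93.5%. This stands.

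**Graded items are a reading.** The article says multiple-choice. That scores are transformed into symptoms supports graded answers, but with only two levels the sum would equal the count and nothing would be gained.

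**Changing a published scoring after data collection invites a charge of outcome switching.** This stands as a real cost, and the remedy must answer it.

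**Conclusion.** The point holds as a loss of sensitivity in one primary outcome. It is neither an error of arithmetic nor a threat to the trial as a whole. The described scoring discards change below the item cut-off, while the power plan gives ADHD the same 0.20 SD effect as a score with mean 100 and SD 15.

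The direction is firm: the sum is about as efficient as the count or better in the scenarios examined, and a diagnosis is clearly worse. The size is not firm, because item levels, cut-off, endorsement and sub-threshold ratings are all assumed. The avoidable loss could be negligible or about 13 points. The change is worth making because it is cheap, uses answers already held, and removes the risk that a diagnosis becomes the main score.

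**What to change.** In the SAP, before database lock and before any analysis by group, name the sum of the 18 graded teacher items, adjusted for its baseline value, as the main ADHD score. Report symptom count, diagnostic criteria and subtypes as secondary. State the item levels and the symptom cut-off.

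The cost is one SAP entry and rescoring of existing answers. There are two downsides:
- The primary ADHD result is no longer in diagnostic units; the secondary results still supply them.
- The Abstract says the data are already collected, so the change must be dated and disclosed as made before analysis. The Discussion says those doing the statistical analyses are blinded to the intervention, which helps to show this.

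The change does not restore the planned power. Any report should say that low symptom levels may still limit what this outcome can show.

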
### Laboratory Determinations

The venipuncture blood collection was done by a nurse at the schools after securing appropriate conditions at baseline and after 6 months of intervention. The red blood cell proportions of omega-3 fatty acids (DHA, EPA and ALA) and omega-6 fatty acids (AA), among other fatty acids, were determined by gas chromatography at baseline and after 6 months of intervention. Details on quality control for this method are described elsewhere (32). The results were expressed in relative amounts (percent of total fatty acids).

### Clinical Evaluation and Other Secondary Measurements

In addition to the neuropsychological and behavioral endpoints, secondary intermediate outcomes of interest were measured at baseline and after 6 months of intervention. We aim to explore whether there are changes in height (in cm), weight (in kg), waist circumference (in cm), and blood pressure. These other health outcomes can be affected by changes in the diet: particularly walnut intake can improve cardiometabolic indicators (33). Height was measured using the stadiometer model SECA 214, weight by the weighing scales SECA 770 model, and waist circumference with the SECA 201 tape model. Blood pressure (systolic and diastolic) were measured (in triplicate) after 5 min of rest with an OMROM 705-CPII device in the dominant arm. All measurements were done by a trained nurse at the schools and followed standard procedures.

Additionally, at baseline, two questionnaires of sociodemographic and clinical characteristics and lifestyle factors were obtained to collect covariables such as parental education and socio-economic level, parental mental health status, sociodemographic characteristics, adolescent health history, and lifestyle habits such as physical activity, sleep duration, and daily screen time exposure. Further estimations of environment and ambient pollution based on home and school geo-localizations were recorded.

Finally, in the same subsample of 270 participants, we collected extra samples of blood and urine before and after the nutritional intervention to assess potential secondary effects of the intervention and also to investigate the biological effects of other important risk factors collected in this study, such as lifestyle factors, environmental exposure, nutritional status, and the mental health status of the participants.

## Data Analysis

Descriptive statistics (frequencies, means, standard deviations for normally distributed data; medians and interquartile ranges for nonparametric data) will be used to describe the baseline characteristics of the walnut and control groups. To assess the effect of the intervention on brain development, we use multivariable linear regression models. Similar regression models will be used to assess the effect of the intervention on red blood cell PUFA proportions, particularly ALA, as outcome variables. To assess the proportion of the effect of the intervention on brain development that is mediated by red blood cell PUFA changes, results will be compared in models with and without the mediator. All analyses will be based on the intention to treat in order to estimate the effectiveness of a public health recommendation (i.e., to encourage eating 30 g of walnuts per day). We also plan to conduct a per-protocol analysis with those who comply with the intervention, i.e., single days of reporting eating walnuts (≥ 100 days during 6 months) (34). The nominal statistical significance will be set at the *P* < 0.05 level (two-sided) for the primary outcomes. Statistical analyses are performed with STATA. A detailed statistical analysis plan will be established before database lock and any analyses.

Using multiple primary endpoints, the study will be considered successful if the results of either one of the primary endpoints is statistically significant in favor of the experimental treatment and/or treatment adherence. In this case, we will report for each primary endpoint a nominally significant level and the corrected *p*-value determined by the method for multiplicity adjustment.

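### The any-one-of-six success rule is not tied to the Benjamini-Hochberg-corrected p-value; read with the only threshold stated, false success in favour of walnuts is about 12.5%

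*Protocol article*

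**What the plan says.** The Data Analysis section of the protocol article makes three statements, in this order.

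- Threshold: "The nominal statistical significance will be set at the *P* < 0.05 level (two-sided) for the primary outcomes".
- Success: the study counts as "successful if the results of either one of the primary endpoints is statistically significant in favor of the experimental treatment". The sentence then adds an and/or alternative that refers to treatment adherence and is not defined.
- Reporting: in that event, "we will report for each primary endpoint a nominally significant level and the corrected" p-value, obtained by a multiplicity method that this section does not name.

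The Sample Size section says "Six primary outcomes were considered" and lists them. On error control it says "We considered a type I error of 0.05 and corrected calculations for multiplicity using the Benjamini-Hochberg method". It then gives power for detecting the effect in at least one, two, three, four, five and all six outcomes: 95%, 90%, 80%, 70%, 55% and 31%.

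**The concern.** A rule that lets any one of six endpoints carry the trial needs a stated significance criterion that allows for six chances. Here the only criterion attached to the primary outcomes is labelled nominal. The corrected p-value has neither a threshold nor a role in the decision. The Sample Size section uses a different and stricter procedure, so the rule for declaring success and the rule behind the power figures do not agree as written.

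At stake is the main claim of the trial. The abstract says the results could be turned into nutritional recommendations for teenagers. A positive verdict could rest on one nominally significant result out of six, with a corrected p-value beside it that does not support it, and the protocol would give no clear ground for calling the trial negative.

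**Working it through.** **Inputs.** From Sample Size: six outcomes, SD 15, correlation 0.25, effect 3 units, 400 per group, 10% loss (so 0.9 × 400 = 360 per group), R-squared 20%, type I error 0.05, BH. From Data Analysis: two-sided nominal 0.05, any one endpoint, result in favour of treatment. Assumed here: equal correlation between all pairs, normal test statistics, and a correlation range of 0 to 0.5 around the stated 0.25.

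**Step 1: which rule do the stated powers reflect?** The standard error of a group difference is 15 × √(2/360) = 1.118, so each test statistic has mean 3/1.118 = 2.68. Six statistics with correlation 0.25 were simulated under each rule.

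| Outcomes detected, at least | Stated | BH | Nominal 0.05 |
|---|---|---|---|
| 1 | 95% | 95.4% | 99.4% |
| 2 | 90% | 90.5% | 97.1% |
| 3 | 80% | 83.3% | 91.3% |
| 4 | 70% | 72.4% | 79.8% |
| 5 | 55% | 55.8% | 60.1% |
| 6 | 31% | 31.4% | 31.4% |

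The last row cannot separate the rules, because BH rejects all six exactly when the largest p-value is at most 0.05. The other rows fit BH and not the nominal rule. The fit is not exact: the third and fourth rows differ from the stated figures by 3.3 and 2.4 points. It also ignores the stated R-squared. With R-squared 20% the SD becomes 15 × √0.8 = 13.42, the mean statistic becomes 3.0, and power for at least one outcome is 98.4% under BH and 99.9% under the nominal rule. That discrepancy is a separate matter.

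**Step 2: false success under the literal rule.** Suppose no outcome is affected. With independent outcomes, the chance that at least one is nominally significant in favour of walnuts is 1 − 0.975⁶ = 14.1%. For correlation ρ it is

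∫ {1 − [1 − q(t)]⁶} φ(t) dt, with q(t) = 1 − Φ((1.96 − √ρ·t)/√(1 − ρ)).

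| Correlation | Nominal, in favour | BH, in favour | Nominal, either direction | BH, either direction |
|---|---|---|---|---|
| 0 (assumed) | 14.1% | 2.6% | 26.5% | 5.0% |
| 0.25 (protocol) | 12.5% | 2.4% | 24.8% | 4.9% |
| 0.5 (assumed) | 10.4% | 2.2% | 20.7% | 4.4% |

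The nominal columns come from the formula (its two-sided version for either direction), the BH columns from simulation. Success requires a favourable result, so the in-favour columns are the relevant ones. At the protocol's correlation the ratio is 12.5/2.4, about five-fold.

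**The case against.** The strongest reply is that the protocol never says the uncorrected p-value decides. The success sentence speaks only of statistical significance, stands in a paragraph about multiple endpoints, and leads directly to the corrected p-value. The Sample Size section names BH and quantifies the same at-least-one criterion with it, and Step 1 supports that. Read this way, the two sections agree and the error is about 5% in either direction. The article also promises a detailed analysis plan before database lock, which may settle the matter.

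Much of this stands. A reader might infer that the protocol openly adopts uncorrected testing; the text does not go that far, and the BH intention in Sample Size is evidence against it. The reply does not remove the point, however. The only level attached to the primary outcomes is labelled nominal, and the corrected p-value is given a reporting role only. Nor is this just a detail left to the analysis plan: the article itself fixes a threshold and a success rule, and together they do not match its own power basis.

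Two larger error figures are also tempting. A reader might quote about 25%, but that counts results in either direction, and the rule requires one in favour of treatment. A reader might also add a second route to success through the adherence clause, for instance the planned per-protocol analysis. The clause is undefined, the section bases its analyses on intention to treat, and no correlation between the two analyses is given, so the documents support no figure for that route.

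**Conclusion.** Wrong as written. The success rule does not tie success to the BH-corrected p-value, and with the only threshold stated it conflicts with the Sample Size section. On that literal reading, false success in favour of walnuts is about 12.5% when no outcome is affected and the correlation is 0.25, and about 10% to 14% over the assumed range of 0 to 0.5, against about 2.4% under BH. If corrected significance was intended throughout, the error rate is acceptable under the global null and the defect is one of wording, which the same sentence cures.

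The result rests on equal correlations, normal test statistics and no true effect on any outcome. That the stated powers reflect BH rests on the Sample Size text and on the approximate match in Step 1, which leaves out R-squared.

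**What to change.** Replace the success sentence, and carry the same wording into the analysis plan before database lock: the trial is successful only if at least one of the six primary endpoints has a Benjamini-Hochberg-adjusted two-sided p-value of 0.05 or less, in favour of walnuts, in the intention-to-treat analysis. Add that nominal p-values are descriptive, and that a per-protocol or adherence result cannot by itself declare success.

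BH holds the chance of any false positive at about 5% when no outcome is affected, but what it controls in general is the false discovery rate. If the sponsor wants to claim strong familywise control, Holm or a similar method is needed, at some cost in power: with 360 per group and SD 15, power for at least two outcomes is 83.5% under Holm against 90.5% under BH.

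The cost is a few sentences, with no change to data or sample size. Success becomes harder to declare than under the nominal reading (95.4% against 99.4% power for at least one outcome in Step 1), but the stated power already assumes BH.
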